# Antibiotic prescribing and non-prescribing in nursing home residents with signs and symptoms ascribed to urinary tract infection (ANNA): study protocol for a cluster randomized controlled trial

**DOI:** 10.1186/s12877-020-01662-0

**Published:** 2020-09-11

**Keywords:** Urinary tract infection, Nursing homes, Antibiotic prescribing, Antibiotic stewardship, Decision support, Randomized controlled trial

## Abstract

**Background:**

Antibiotic overprescribing for suspected urinary tract infection (UTI) in nursing homes (NHs) is common. Typical clinical scenarios in which antibiotics are inappropriately prescribed include response to nonspecific signs and symptoms and/or a positive urine test in the absence of symptoms referable to the urinary tract. These and other scenarios for inappropriate antibiotic prescribing were addressed in a recent international Delphi study which resulted in the development of a decision tool for the empiric treatment of UTI in frail older adults. The aim of the current study is to implement this decision tool, by integrating it into the electronic health record (EHR) and providing education on its content and use, and to evaluate its effect on appropriate antibiotic prescribing. An additional aim is to evaluate the quality of the intervention and the implementation process.

**Methods:**

A cluster Randomized Controlled Trial (cRCT) is conducted in sixteen NHs and aims to include 897 residents diagnosed with suspected UTI. NHs in the intervention group use the EHR-integrated decision tool, and receive education for physicians and nursing staff; in the control group care as usual is provided. Data is collected through case report forms within the EHR at the day of diagnosis and at 3, 7, and 21 days thereafter. The primary outcome is appropriate antibiotic prescribing for suspected UTI at the day of diagnosis. Secondary outcomes include the course of symptoms, alternative diagnoses, treatment changes, complications, hospitalization, and mortality. Data on total antibiotic prescribing are additionally collected in the participating NHs 12 months before and during the study. Finally, the process evaluation combines cRCT data with questionnaires and qualitative interviews with NH professionals.

**Discussion:**

This is the first cRCT to evaluate the recently developed, international decision tool for empiric treatment of suspected UTI in NH residents. Study findings will elucidate the effect of the intervention on appropriate antibiotic prescribing for suspected UTI, and provide insight into the applicability of the decision tool in NHs in general and in specific subgroups of NH residents. With this study we aim to contribute to antibiotic stewardship efforts in long-term care.

**Trial registration:**

The ANNA study was registered at the Netherlands Trial Register on 26 February 2019, with identification number NTR NL7555.

## Background

Urinary tract infections (UTIs) are common among nursing home (NH) residents and account for the largest share of antibiotic prescribing in this setting [1]. Diagnosing UTIs is challenging in the NH population because presenting symptoms are often not typical and cognitive disabilities can impede communication of experienced complaints. This diagnostic uncertainty, in combination with other factors such as expectations of residents and their family members, drives antibiotic prescribing to be ‘better safe than sorry’ [2].

A substantial part of the antibiotics prescribed for suspected UTI in NHs, however, is considered inappropriate [3]. There are two common situations in which this is the case. The first is for nonspecific signs and symptoms (eg, mental status change or behavioral problems); these are often not attributable to UTI but to one of many other possible causes [4]. Second, antibiotics are frequently prescribed in response to a positive urine test (eg, a dipstick test) [5–8]. There is a high a priori chance of positive test results due to the up to 50% prevalence of asymptomatic bacteriuria in the NH setting, a condition for which antibiotics are not indicated [9–12]. Urine testing is therefore considered only useful to rule out UTI when the results are negative, but otherwise should not influence treatment decisions [4].

Inappropriate antibiotic use is an important problem. For the individual, inappropriate antibiotic use is associated with an increased risk of unnecessary exposure to side-effects and drug interactions. In addition, inappropriate antibiotic use may be accompanied by under-treatment of other conditions, if no further assessment is done to look for alternative causes that may underlie the signs and symptoms ascribed to UTI. On the societal level, inappropriate antibiotic use plays an important role in the development of antibiotic resistance [1].

In order to improve appropriateness of antibiotic prescribing in NHs, a decision tool to support medical decision making in frail older adults with a possible UTI was recently developed in an international Delphi study [4]. Here we describe the protocol of a cluster Randomized Controlled Trial (cRCT) in which this decision tool is implemented in NHs by incorporating it into the electronic health record (EHR), and by educating professionals on its content. The first objective of the study is to evaluate whether this results in more appropriate antibiotic prescribing for NH residents with suspected UTI. In addition, we evaluate the quality of the intervention and the implementation process.

## Methods

The Antibiotic prescribing and Non-prescribing in Nursing home residents with signs and symptoms Ascribed to urinary tract infection (ANNA) study aims to evaluate, in a cRCT, the effect of an EHR-integrated decision tool in combination with education, on the appropriateness of antibiotic prescribing for NH residents with suspected UTI. In addition, it aims to evaluate the quality of the intervention and the implementation process in a process evaluation.

### Cluster randomized controlled trial

Table 1 provides a schematic overview of resident enrollment, intervention, and data collection (ie, SPIRIT schedule).

**Table 1 Tab1:** SPIRIT schedule of resident enrollment, intervention, and data collection

	Allocation	Enrolment	Data collection				Close-out
TIMEPOINT	Before study onset	T0 (index)	T0 (index)	T1 (day 3)	T2 (day 7)	T3 (day 21)	After completion data-collection
**ENROLMENT**							
***Eligibility screen***		X					
***Informed consent***	X						
***Allocation***	X						
**INTERVENTIONS**							
***UTI treatment decision tool in EHR***		X	X				
***Education for physicians & nursing staff***	X						
**ASSESSMENTS**							
***Patient characteristics***			X				
***Primary outcome*** *(appropriate antibiotic prescribing)*			X				
***Secondary outcomes*** *(course of symptoms, alternative diagnoses, changes in treatment policy, hospitalization, morality)*			X	X	X	X	
***Total antibiotic prescribing***							X

*Abbreviations: UTI* Urinary tract infection*, EHR* Electronic health record

#### Study design and setting

A cRCT is conducted with NHs as the unit of randomization. Although our sample size calculation (see below) required the inclusion of fifteen NHs in the study, a total of sixteen NHs across the Netherlands participate in the study. Data collection has started in March 2019 and lasts approximately 1 year.

Residents of Dutch NHs typically reside on somatic wards (ie, for residents with mainly physical conditions); psychogeriatric wards (ie, for residents with cognitive disabilities such as dementia); or geriatric rehabilitation wards. Due to high turn-over rates, geriatric rehabilitation wards are excluded from the study. Unique to Dutch NHs is that medical care is mainly provided by specialized ‘elderly care physicians’. Elderly care physicians are employed by, and have their main site of practice in the NH, although they increasingly also provide care for frail older persons living at home [13]. Other providers of medical care, similarly employed by the NH, may include physicians with other specializations (eg, geriatrics, family medicine), junior doctors, elderly care physicians in training, and nurse practitioners. Where the word ‘physician’ is used in this paper, we refer to all these medical care providers.

#### Informed consent procedure

Before study onset, all residents (or their representatives, in case of legal incapacity) of participating NH wards received written information about the study and an informed consent form. During the study, all newly admitted residents similarly receive this information and informed consent form. Consent is asked for participation in the study in case a resident develops a suspected UTI during the study period and is eligible for inclusion (ie, pre-emptive consent). Consent is also asked for using their data in ancillary studies. In addition to the written information, NH physicians provide residents with verbal information on the study during regular contact moments.

#### In- and exclusion criteria

NH residents are included in the study if they are diagnosed with suspected UTI and provided informed consent. Excluded are residents who are already taking antibiotics or have taken antibiotics in the previous 7 days, and residents who do not wish to be treated with antibiotics in case of a UTI.

#### Sample size

We consider an increase of at least 20% appropriate antibiotic prescribing for suspected UTI to be clinically relevant (ie, based on previous research from our group, from 66% in the control group to 86% in the intervention group) [14]. To detect this difference with 80% power and a significance level of 5%, 72 cases of antibiotic prescribing for UTI would be required in each group [15]. Based on previous study data [14], we expect that antibiotics will be prescribed in 91% of cases of suspected UTI in the control group, and that our intervention has the potential to reduce this to 62% of suspected UTI in the intervention group. Consequently, 79 cases of suspected UTI are required in the control group to include 72 antibiotic prescriptions, and up to 116 in the intervention group.

Dutch NHs possess approximately 150 beds, per location, on average. Dutch surveillance studies report an incidence rate of 87 UTIs per 150 beds per year [16]. Based on prior, comparable research [14], we estimate that 70% of the residents (or their representatives in case of legal incapacity) provides informed consent to participate in the study, which converts to 61 recruited residents per 150 beds per year for the present study.

Corrected for clustering within NHs, we need (79 × 4.6=) 363 cases in the control group and (116 × 4.6=) 534 in the intervention group (design effect: 1 + ((cluster size − 1) x intraclass correlation coefficient) = 1 + ((61–1) × 0.06) = 4.6). The estimate of the intraclass correlation coefficient is based on Campbell et al and prior study data [14, 17].

To include 363 cases over a period of 12 months, (363/61) 6 NHs are required in the control group. To include 534 cases over a period of 12 months, (534/61) 9 NHs are required in the intervention group.

Figure 1 provides a flow diagram with the intended number of participants.

**Fig. 1 Fig1:**
[figure not shown]
Flow diagram with the intended number of participants

#### Intervention

##### Decision tool

When a physician reports pre-structured clinical information in the EHR of residents with a suspected UTI and who provided informed consent, the decision tool automatically generates a treatment advice. The physician is free to deviate from the treatment advice and remains responsible for the treatment decision. All physicians receive a pocket card of the decision tool for situations without access to the EHR (and therefore to the decision tool).

##### Physician education

Physician education consists of: 1) a one-hour interactive presentation about the content of the decision tool, provided by the research team, and 2) a role play to learn how to deal with pressure to prescribe antibiotics from residents, their family or nursing staff, and on how to train nursing staff on the content of the decision tool.

##### Nursing staff education

The complete nursing staff is offered a 6-min video about dealing with suspected UTI in NH residents (based on a training module developed by prof. [name] and his research group, University of North Carolina at Chapel Hill). In this video, particular attention is paid to standardized assessment of residents with suspected UTI and to other common causes of non-specific signs and symptoms. A part of the nursing staff (ie, at least one nurse per ten residents) additionally completes a 20-min e-learning to become ‘experts’ with sufficient knowledge for education of other nursing staff. In the e-learning, the video topics are discussed in more detail. Furthermore, attention is paid to how to deal with pressure from residents or their family asking for urine analysis or an antibiotic prescription. After finishing the e-learning, ‘experts’ receive a pocket card with a summary of the e-learning content. Finally, information material on actively monitoring residents who are not prescribed antibiotics, is provided to nursing staff for distribution to residents and/or their family members.

#### Control group

In the control group, care as usual is provided without any restrictions.

#### Randomization and blinding

A block randomization procedure was performed by an independent individual using randomization software. Since physicians in the intervention group use the decision tool, and the research team provides education to physicians and nursing staff, blinding of NH professionals and the research team was not feasible.

#### Data collection

##### Research application

Both in the intervention and control group, data is collected through a research application integrated in the EHR. The application starts automatically when a physician enters the diagnosis suspected UTI in the EHR of a resident that provided informed consent. This reduces chances of missing potential inclusions. To foster the collection of correct and complete data, the research application is designed in such a way that only realistic values can be entered and that case report forms (CRFs) can only be submitted if all questions regarding symptomatology and treatment have been answered.

##### Collected data

The period of data collection for each participant is 3 weeks from the day of diagnosis. The first CRF that pops up comprises in- and exclusion criteria for participation in the study. If a resident is eligible to participate, a new CRF (T0) appears that includes resident characteristics (ie, sex and age), co-morbidities (eg, dementia, urinary tract abnormalities), and index consultation data such as signs and symptoms (specific, nonspecific and systemic), additional diagnostics (eg, urine analysis) and treatment (eg, whether antibiotics were started or not). The application automatically generates follow-up CRFs to be completed on day 3 (T1), 7 (T2) and 21 (T3). In addition to EHR-generated data, anonymous data on total antibiotic prescribing in the NH is collected in the 12 months before and during the study.

##### Outcomes

The primary study outcome is appropriate antibiotic prescribing for suspected UTI at index consultation (yes/no), ie, prescribing in compliance with the treatment advice generated by the decision tool. Secondary study outcomes include the course of symptoms after the index consultation (ie, recovery, unchanged or deterioration), alternative diagnoses after assessment, changes in treatment policy (eg, start/stop antibiotics, adjustments in dose, type or duration) and motivation for these changes, complications, hospitalization, mortality and total antibiotic prescribing on the NH level.

##### Analysis

The primary analysis assesses the difference between the intervention and the control group in appropriate antibiotic prescribing for suspected UTI, treated with antibiotics, at index consultation. A three level logistic regression model is used to account for variation at the NH/physician/resident level. lf there is no indication of random effects at the physician level, the three level logistic multilevel regression model is reduced to a two level model. Multilevel regression modeling is similarly used to compare secondary study outcomes between the two groups (linear or logistic, as appropriate). A second-order penalized quasi-likelihood estimation procedure is applied, using MLwiN software. Data on total antibiotic prescribing in the 12 months prior to the start of the study, and during the study period is explored descriptively in order to describe the potential impact of adjusted antibiotic prescribing for UTI on total antibiotic prescribing within intervention NHs, compared to control NHs.

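### The primary analysis keeps only antibiotic-treated cases, a post-randomisation group the intervention is expected to change, so it does not compare the randomised groups and cannot count decisions to withhold

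*Protocol article*

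**What the plan says.** All places are in the Methods of the protocol article.

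- **Inclusion (In- and exclusion criteria).** "NH residents are included in the study if they are diagnosed with suspected UTI and provided informed consent". Being treated is not a condition of entry. The Background and the Discussion also state the aim for residents with suspected UTI.
- **Outcome (Outcomes).** "The primary study outcome is appropriate antibiotic prescribing for suspected UTI at index consultation (yes/no), ie, prescribing in compliance with the treatment advice". The advice meant is that of the decision tool. No restriction to treated cases is stated.
- **Primary analysis (Analysis).** The arms are compared "in appropriate antibiotic prescribing for suspected UTI, treated with antibiotics, at index consultation", with a three-level logistic model that may be reduced to two levels.
- **Planning (Sample size).** Appropriateness is to rise "from 66% in the control group to 86% in the intervention group", described as the smallest relevant gain, and "72 cases of antibiotic prescribing for UTI would be required in each group". For usual care, the section expects that "antibiotics will be prescribed in 91% of cases of suspected UTI in the control group". For the other arm it plans on a lower share, because "our intervention has the potential to reduce this to 62% of suspected UTI in the intervention group".
- **Other outcomes (Outcomes; Process evaluation).** Course of symptoms, treatment changes, complications, hospitalisation and mortality are secondary and are compared between arms. Compliance with the advice and reasons for deviating from it are collected as indicators of intervention quality.

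**The concern.** Whether a resident receives antibiotics is decided after allocation, and the intervention is built to change that decision. Restricting the primary analysis to treated cases compares two groups that the intervention itself has helped to select. The multilevel model handles clustering but does not restore the randomised comparison.

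The restriction also removes every decision to withhold, right or wrong, from the primary result. The proportion appropriate among treated cases can rise because unneeded prescriptions disappear, because some residents advised treatment go untreated alongside them, or both. The endpoint cannot tell these apart. The protocol's objective is better prescribing for residents with suspected UTI, and its Discussion says that the tool is unvalidated and its consequences for resident safety have not been investigated. What is at stake is whether a significant primary result could be read as better decisions.

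**Working it through.** **1. The plan's own sample size.** Inputs: 66% vs 86%, 80% power, 5% two-sided (sidedness is not stated, but the stated number fits two-sided). The pooled-variance formula without continuity correction gives 71 per group; the plan states 72, at which power is 80.9%. Then 72/0.91 = 79.1 and 72/0.62 = 116.1 suspected UTIs. The design effect is 1 + 60 × 0.06 = 4.6, so 79 × 4.6 = 363 and 116 × 4.6 = 534, total 897. The arithmetic is sound for a treated-only analysis, which shows that the restriction is deliberate.

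**2. Cases dropped.** Control: 1 − 0.91 = 9%. Intervention: 1 − 0.62 = 38%. The planned difference is 29 points.

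**3. Prescriptions per 100 suspected UTIs if 62% treated and 86% appropriate hold together.**

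| | Control | Intervention | Change |
|---|---|---|---|
| Appropriate | 91 × 0.66 = 60.1 | 62 × 0.86 = 53.3 | −6.7 |
| Inappropriate | 91 × 0.34 = 30.9 | 62 × 0.14 = 8.7 | −22.3 |

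With the same case mix in both arms, 6.7 more per 100 intervention cases would be advised antibiotics and not receive them, about 0.0674 × 534 = 36 residents. The primary result would show +20 points.

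**4. All-case agreement with the advice.** Let π be the share of cases for which the tool advises treatment, T the share treated and A the share appropriate among the treated. Assume that every case has one advice (treat or do not treat) and that π is equal in both arms. Then

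agreement = T·A + (1 − π) − T·(1 − A).

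The protocol does not give π. Its control figures bound it: at least 0.6006, and at most 1 − 0.3094 = 0.6906. Agreement is then 69.1% vs 84.6% at π = 0.6006 and 60.1% vs 75.6% at π = 0.6906. The difference does not depend on π: (0.5332 − 0.6006) − (0.0868 − 0.3094) = 0.155.

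**5. Sensitivity to the pairing.** The shortfall in appropriate prescriptions is zero when T × 0.86 = 0.6006, that is T = 69.8%. At that value the all-case gain is (0.6003 − 0.6006) − (0.0977 − 0.3094) = 0.211. With 62% treated, the shortfall is zero when A = 0.6006/0.62 = 96.9%.

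**6. Power of the all-case analysis.** Inputs: 6 and 9 NHs of 61 cases, so effective sizes are 366/4.6 = 79.6 and 549/4.6 = 119.3; unpooled variance; range over π.

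| All-case gain | Normal reference | t reference, 13 df |
|---|---|---|
| 15.5 points | 63–71% | 57–65% |
| 21 points | 90–95% | 85–92% |

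**7. What the endpoint cannot see (hypothetical, π = 0.6006).** An arm that treated half of those advised treatment and nobody else would score 100% on the treated-only analysis. Its all-case agreement would be 0.3003 + 0.3994 = 70.0%, against 69.1% in control. The plan projects no such arm; the example only shows a property of the measure.

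**The case against.** Four objections carry weight.

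- **Consistency.** A reader might infer that the analysis contradicts the stated outcome. That is too strong. Prescribing in compliance with the advice can mean prescriptions only, and the sample size is built on the same treated set as the analysis. The outcome sentence is ambiguous.
- **Magnitude.** A reader might infer that at least 6.7 per 100 residents with an indication would go untreated, or that an all-case analysis is necessarily underpowered. The documents support neither. The 86% comes from a minimum relevant gain, while the 62% is a reduction the intervention has the potential to reach. Pairing them gives one scenario and not a bound; step 5 shows the shortfall vanishing under modest changes.
- **Monitoring.** A reader might infer that the trial is blind to under-treatment. That is true only of the primary analysis. The secondary outcomes can show clinical consequences, and compliance is collected for the process evaluation. However, the article states no between-arm comparison of withholding against advice.
- **Remedy.** Suspected UTI is diagnosed after allocation by unblinded physicians, and staff education may alter who is suspected. An all-case set therefore keeps some selection. Data collection also began in March 2019 for about a year and the article appeared in September 2020, so replacing the primary analysis is more than a change of wording.

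These objections narrow the claim and shape the fix. None removes the conditioning on treatment.

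**Conclusion.** The point holds in this form. The primary analysis conditions on a post-randomisation event that the plan expects to differ by 29 points because of the intervention. It therefore does not compare the randomised groups, and it leaves every decision to withhold out of the headline result. As it stands, a significant result would support a statement about prescriptions given, not about decisions for residents with suspected UTI.

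The numerical consequence depends on the scenario. Set beside the 20-point primary gain, the all-case gain is 15.5 points if 62% treated and 86% appropriate occur together, and about 21 points, with no fall in appropriate prescriptions, if 69.8% are treated at 86%. Both figures assume the same share advised treatment in each arm and a single treat or do-not-treat advice per case. Neither predicts the trial's result, and the protocol does not show that indicated treatment would be withheld.

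**What to change.** - **Population and outcome.** Analyse all included suspected UTIs. Define appropriate as agreement of the index decision, prescribe or withhold, with the tool's advice computed from the T0 form in both arms.
- **Status.** Make this the primary analysis if the plan can still be changed before results by arm are seen. Otherwise prespecify it as the key secondary analysis, which must agree before improved decisions for suspected UTI are claimed.
- **Treated-only analysis.** Keep it as supportive, or as primary with its conclusion limited to prescriptions given.
- **Reporting.** Give by arm, per 100 suspected UTIs, the numbers prescribed against advice and withheld against advice. Compare the number of suspected UTIs and their case mix by arm, because diagnosis is unblinded and follows allocation.
- **Outcome wording.** State whether the primary outcome covers all index decisions or prescriptions only.

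**Cost.** The T0 form already records signs, symptoms, diagnostics and whether antibiotics were started, so no new data are needed. Power must be restated as a range: about 63–71% at a 15.5-point gain to about 90–95% at 21 points (normal reference, 6 + 9 NHs, design effect 4.6), and lower with a t reference. The timing and reason of any change of primary analysis must be documented.

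### Sixteen randomized nursing homes with no small-cluster adjustment: if the arm effect is tested by a normal-reference Wald test, the nominal 5% level is about 7% to 9% at the planned ICC

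*Protocol article*

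**What the plan says.** Protocol article, Study design and setting: "A cRCT is conducted with NHs as the unit of randomization", and "a total of sixteen NHs across the Netherlands participate in the study". The sample size calculation asked for fifteen, 6 control and 9 intervention. How the sixteen divide between the arms is not stated in the text.

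Protocol article, Sample size: "To detect this difference with 80% power and a significance level of 5%, 72 cases of antibiotic prescribing for UTI would be required in each" arm, for a rise "from 66% in the control group to 86% in the intervention group". The count is then multiplied by a design effect of 4.6 (cluster size 61, ICC 0.06). Nothing is added for the small number of clusters.

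Protocol article, Analysis: the primary comparison is made among cases treated with antibiotics. It uses a logistic model with NH, physician and resident levels, which may drop to two levels. Multilevel models are also used for secondary outcomes, except that total antibiotic prescribing is only described. On estimation the text reads: "A second-order penalized quasi-likelihood estimation procedure is applied, using MLwiN software". It does not state the test statistic, the reference distribution, the degrees of freedom, or whether estimation is ML-type (IGLS) or restricted (RIGLS).

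**The concern.** Treatment varies only between NHs. However many residents are enrolled, the precision of the arm contrast is judged from the spread of about sixteen NH-level results. A physician level in the model does not change this.

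Two things then go wrong if an ordinary Wald test is used. The between-NH variance is itself estimated on about 14 degrees of freedom, so the ratio of estimate to standard error has heavier tails than the normal. ML-type estimation also biases that variance downward when clusters are few. Quasi-likelihood supplies no true likelihood, so a likelihood-ratio test is not a sound way round this, and the Wald test is the natural one to run.

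At stake is the claimed 5% level for the primary contrast, and the width of the confidence intervals for every contrast taken from these models.

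**Working it through.** **Reproducing the plan's figure.** With 66% and 86%, two-sided 5% and 80% power, the normal-approximation formula with pooled variance gives n = [1.960·√(2·0.76·0.24) + 0.842·√(0.66·0.34 + 0.86·0.14)]² / 0.20² = (1.184 + 0.494)² / 0.04 ≈ 70.4, so 71 against the stated 72. Then:
- 72/0.91 = 79 and 72/0.62 = 116 suspected cases
- design effect 1 + 60 × 0.06 = 4.6
- 79 × 4.6 = 363 and 116 × 4.6 = 534, total 897
- 363/61 → 6 NHs and 534/61 → 9 NHs

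The figure is a normal-quantile calculation times a design effect.

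**Analytic size of the problem.** With 16 NHs, df = 16 − 2 = 14.
- Restricted variance read against 1.96: 2·P(t₁₄ > 1.960) = 7.0%.
- ML variance, smaller by a factor of about 14/16: 2·P(t₁₄ > 1.960·√(14/16)) = 2·P(t₁₄ > 1.833) = 8.8%.
- With 15 NHs (13 df) the same two figures are 7.2% and 9.1%.

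**Simulation under no effect.** A two-level random-intercept logistic model was fitted by purpose-written second-order PQL code (not MLwiN). Inputs from the Sample size section: probability 0.66; ICC 0.06, taken on the probability scale; and treated cases per NH of 61 × 0.91 ≈ 55 (control) and 61 × 0.62 ≈ 38 (intervention), since "antibiotics will be prescribed in 91% of cases of suspected UTI in the control group" and the intervention might "reduce this to 62% of suspected UTI in the intervention group". The splits of the sixteen NHs are assumed. There were 40,000 trials per split (20,000 for 6+9). At 7% and 40,000 trials the Monte Carlo standard error is √(0.07·0.93/40,000) ≈ 0.13 percentage points.

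| NHs | ML-type, 1.96 | Restricted, 1.96 | ML-type, t | Restricted, t | NH-level t-test |
|---|---|---|---|---|---|
| 8+8 | 8.7% | 7.0% | 6.4% | 5.0% | 5.1% |
| 7+9 | 8.8% | 7.1% | 6.6% | 4.9% | 4.8% |
| 6+10 | 8.9% | 7.0% | 6.5% | 5.1% | 4.8% |
| 6+9 | 9.0% | 7.2% | 6.6% | 5.0% | 4.9% |

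A separate simulation with 55 cases in every NH (3,000 runs per design) agrees: 8.7–9.2% (ML-type, normal), 6.6–7.1% (restricted, normal) and 4.8–5.1% (restricted, t).

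**Sensitivity, normal reference, restricted / ML-type.**
- Unequal NH sizes (assumed CV 0.5): 6.9–7.3% / 8.8–9.4%
- Assumed ICC 0.03: 6.5% / 8.2%
- Assumed ICC 0.02: 5.9% / 7.1%
- Assumed ICC 0.01: 5.8% / 6.9%
- Assumed ICC 0.02 with only 15–20 cases per NH: 5.0% / 6.1%

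**Cost in interval width.** 2.145/1.960 = 1.09 (14 df); 2.160/1.960 = 1.10 (13 df).

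**Cost in power.** At the plan's design effect, Var = 4.6 × [0.66·0.34/(J₀·61·0.91) + 0.86·0.14/(J₁·61·0.62)], where J₀ and J₁ are the numbers of control and intervention NHs, and the noncentrality is 0.20/√Var.
- 6+9: Var = 4.6 × (0.000674 + 0.000354) = 0.00473, noncentrality 2.91. Power with t₁₃ is 77%. With a normal reference it would be about Φ(2.91 − 1.96) = 83%.
- 6+10: 79%. 7+9: 81%. 8+8: noncentrality 3.10, power 82%.

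The factor of 4.6 uses all 61 suspected cases per NH, whereas the primary analysis uses treated cases only. With 55 and 38 per NH the design effects are 1 + 54 × 0.06 = 4.24 and 1 + 37 × 0.06 = 3.22, and power with t is 83% (6+9), 85% (6+10), 87% (7+9) and 89% (8+8).

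**The case against.** The strongest reply is that the article names no reference distribution. A t reference can be applied to the same PQL estimate and standard error, and an analysis plan that is not shown may do so. This stands in part: the error rates are conditional on a normal-reference Wald test, and a reader who infers that the protocol prescribes such a test, or that the trial's true false-positive rate is 7% to 9%, goes beyond the text. But the article goes past the usual summary. It fixes the model, the order of the approximation and the software for sixteen randomized units, and makes no small-cluster adjustment in either the analysis or the sample size. Running that procedure in the ordinary way misses the stated level.

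Four further inferences are tempting, and the material does not support them:
- **That quasi-likelihood is to blame.** Second-order PQL with restricted variance and a t reference holds about 5% in the table above, so the quoted sentence is not itself the error.
- **That every secondary comparison is affected.** Total antibiotic prescribing is described without a test. The simulations cover a binary outcome near 66%, not rare events such as death, and not linear models.
- **That the 7% to 9% range is firm.** The upper end needs ML-type estimation, which the article does not state, and both ends need a realised ICC near the planning value of 0.06.
- **That correcting the test leaves 80% power intact.** On the plan's own design effect that depends on the split of NHs.

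**Conclusion.** The point holds in conditional form. With sixteen NHs, a normal-reference Wald test from the named procedure has a type I error of about 7% (restricted variance) or about 9% (ML variance) at ICC 0.06, and about 5% to 7% at an ICC of 0.01 to 0.02. On 14 df, a normal-based p value between about 0.032 (the two-sided normal p at 2.145) and 0.05 would be called significant without reaching the 5% level.

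The rates assume a two-level model, a binary outcome near 66% and the planned cluster sizes. The physician level was not simulated, because the article gives no physician counts or variance, and MLwiN itself was not run.

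**What to change.** Add one sentence to the analysis plan: the primary contrast and the model-based secondary contrasts are estimated with RIGLS and tested against t with (number of NHs − 2) degrees of freedom, less one per NH-level covariate, and 95% confidence intervals use the same reference. Both parts are needed, since a t reference with IGLS still gives 6.4% to 6.6%.

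A prespecified NH-level t-test or a permutation test over NH allocations is an acceptable alternative. It is not equivalent, because it may weight NHs differently and target a different quantity, so one should be named as confirmatory in advance.

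The cost is intervals 9% to 10% wider, and power that should be restated on this basis: about 77% (6+9 NHs) to 82% (8+8) at the design effect of 4.6, or about 83% to 89% if the design effect uses treated cases per NH. No change to data collection is needed.
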